## Abstract

TBM is the most severe form of tuberculosis. Clinical trial data are required to provide an evidence base for adjunctive dexamethasone in HIV-positive individuals with TBM, and to guide clinical practice. This document details the planned analyses at 12 months post randomisation for the ACT HIV clinical trial (NCT03092817); ‘a randomised double-blind placebo-controlled trial of adjunctive dexamethasone for the treatment of HIV co-infected adults with tuberculous meningitis (TBM)’. The primary endpoint of the ACT HIV trial is death (from any cause) over the first 12 months after randomisation. This statistical analysis plan expands upon and updates the analysis plan outlined in the published study protocol.

## Scope of document

This document details the planned analyses at 12 months post randomisation for the ACT HIV clinical trial (NCT03092817); ‘a randomised double-blind placebo-controlled trial of adjunctive dexamethasone for the treatment of HIV co-infected adults with tuberculous meningitis (TBM)’. A further analysis will follow at 24 months post randomisation. This statistical analysis plan expands upon and updates the analysis plan outlined in the published study protocol
^
1
^.

## Background and rationale for study

The ACT HIV clinical trial is a randomised double-blind placebo-controlled trial of adjunctive dexamethasone for the treatment of tuberculous meningitis (TBM) in HIV-positive adults. TBM is the most severe form of tuberculosis, with mortality approaching 50% in people living with HIV
^
2–
5
^ despite the best available appropriate anti-TB chemotherapy.

TBM develops when
*Mycobacterium tuberculosis*, initially acquired via the respiratory route, disseminates via the blood to form a secondary focus in the brain. Rupture of this secondary focus into the subarachnoid space results in TBM, with the consequent host inflammatory response being important for bacterial killing, but also responsible for the pathological complications and often-fatal consequences of the infection.

Adjunctive anti-inflammatory corticosteroid therapy, which may control excessive host inflammation, has long been considered to have a role in TBM treatment
^
6
^. In 2004, a landmark clinical trial in Vietnam demonstrated that a 6–8 week (duration dependent on Modified Research Council [MRC] TBM severity grade) tapering course of dexamethasone reduced mortality in adults and adolescents with TBM
^
4
^. In this study, only 98/545 (18.0%) individuals were HIV positive, which was too small to determine if dexamethasone benefited this important sub-group of patients. No other trials have been published since 2004 that examine whether corticosteroids improve outcomes from TBM in HIV-positive adults.

How dexamethasone might confer its clinical benefit on those with TBM remains uncertain. A recent study of cerebrospinal fluid (CSF) cytokines in TBM suggested that HIV-positive individuals have higher cytokine concentrations than HIV-negative individuals
^
7
^. Whether adjunctive dexamethasone is more or less likely to be beneficial in HIV-positive individuals with TBM is not known. There are an estimated 100,000 cases of TBM globally each year
^
8
^, many associated with HIV. Clinical trial data are required to provide an evidence base for adjunctive dexamethasone in HIV-positive individuals with TBM, and to guide clinical practice.

## Structure and status of trial

The ACT HIV trial commenced recruitment on 25
^th^ May 2017. By April 29
^th^ 2021, the predefined sample size of 520 adults with TBM and HIV co-infection had been enrolled from four hospitals in Vietnam and Indonesia: the Hospital for Tropical Diseases (HTD) and Pham Ngoc Thach Hospital for Tuberculosis and Lung Disease (PNT) in Ho Chi Minh City, Vietnam, and Cipto Mangunkusumo Hospital and Persahabatan Hospital in Jakarta, Indonesia. Detailed enrolment criteria for ACT HIV, including consent and ethical approvals, are described in the published trial protocol
^
1
^.

Once enrolled, study participants were randomised to dexamethasone or placebo (a double-blinded allocation), with this intervention termed ‘study drug’. Randomisation was stratified by TBM MRC severity score and by hospital. Participants with MRC grade 1 TBM received a 6-week tapering course of study drug, whereas participants with MRC grades 2 or 3 received an 8-week tapering course of study drug. Study drug regimens are shown in
Table 1. Participants then underwent clinical assessments at baseline, at days 3, 7, 10, 14, 21, and 30, monthly until month 12, and then 3-monthly until 24 months. Baseline assessment included blood tests, chest X-ray, lumbar puncture, and brain imaging.

**Table 1. T1:** Study drug treatment regimen following randomisation.

	MRC Grade I Daily dexamethasone dose/route	MRC Grades II and III Daily dexamethasone dose/route
Week 1	0.3 mg/kg/24 hrs IV	0.4 mg/kg/24 hrs IV
Week 2	0.2 mg/kg/24 hrs IV	0.3 mg/kg/24 hrs IV
Week 3	0.1 mg/kg/24 hrs IV	0.2 mg/kg/24 hrs IV
Week 4	3mg/24 hrs oral	0.1 mg/kg/24 hrs IV
Week 5	2mg/24 hrs oral	4 mg/24 hrs oral
Week 6	1 mg/24 hrs oral	3 mg/24 hrs oral
Week 7	Stop	2 mg/24 hrs oral
Week 8		1 mg/24 hrs oral

IV=intravenous. MRC=Modified Research Council.

ACT HIV has numerous sub-studies, as described in the protocol
^
1
^. Key follow up outcomes include survival, disability, and severe adverse events; especially neurological events, events requiring corticosteroids, HIV-associated complications (malignancies, immune reconstitution inflammatory syndrome [IRIS]), and adverse events considered related to dexamethasone.

## Trial endpoints

### Primary endpoint

The primary endpoint of the ACT HIV trial is death (from any cause) over the first 12 months after randomisation.

### Secondary endpoints

The secondary endpoints of the ACT HIV trial are as follows:

1. Neurological disability at 12 months from randomisation

2. First new neurological event or death over the first 12 months after randomisation

3. Neurological IRIS events over the first 6 months after randomisation

4. New AIDS-defining event or death over the first 12 months after randomisation

5. HIV-associated malignancy by 12 months from randomisation

6. Use of open-label corticosteroid treatment for any reason over the first 12 months after randomisation

7. Requirement for shunt surgery by 12 months

8. Any serious adverse events reported by 12 months from randomisation

## Individuals included in analysis

### Primary analysis

The primary analysis includes all randomised participants. As such, an intention-to-treat (ITT) analysis will be performed for the primary and secondary endpoints. Participants will remain included in this analysis even if no study drug was received after randomisation.

### Per protocol analysis

The per protocol (PP) analysis includes all randomised patients with the exception of those subsequently found to have not met all inclusion criteria, or to have met any exclusion criteria, at the time of enrolment, those with a final diagnosis other than TBM (confirmed by microbiology, serology, or histopathology), and those who received less than 7 days of administration of the randomised study drug for reasons other than death, or less than 30 days of anti-tuberculosis drugs for any reason other than death. Trial inclusion and exclusion criteria are listed in the trial protocol
^
1
^. A per protocol analysis will be performed for all primary and secondary endpoints.

## Statistical software

Data will be analysed using the program R
^
9
^, using the most up to date version available at the time of final analysis.

## Baseline characteristics

Definition: The following baseline characteristics will be summarised by treatment arm for ITT and PP analyses: age, sex, country, site, diagnostic category (definite, probable, possible, or not TBM by Marais criteria
^
10
^), history of previous tuberculosis treatment, chest X-ray findings (no TB/miliary TB/pulmonary TB), enrolment MRC TBM grade, enrolment Glasgow coma score (GCS), weight (kg), duration of symptoms, cranial nerve palsy, hemiplegia, para/tetraplegia, urinary retention, history of diabetes, HbA1c, history of intravenous drug use, hepatitis B sAg positivity, hepatitis C Ab positivity, alanine aminotransferase (ALT), bilirubin, full blood count (haemoglobin, white cell count, platelets), plasma sodium,
*leukotriene A4 hydrolase* (
*LTA4H*) genotype (CC/CT/TT), routine CSF parameters (opening pressure, total leucocytes, total neutrophils, total lymphocytes, protein, blood:CSF glucose ratio, Ziehl-Neelsen stain, Gene Xpert MTB/RIF, Gene Xpert MTB/RIF Ultra, mycobacterial culture), duration of anti-tuberculosis chemotherapy (days) before enrolment, enrolment anti-TB regimen, anti-TB drug susceptibility results in culture-confirmed sub-group (multi-drug resistant [MDR] TB or rifampicin mono-resistant TB, isoniazid resistant non-MDR, pre-extensively drug resistant [XDR] TB, XDR TB, no or other resistance), HIV infection (new or known diagnosis), anti-retroviral therapy (ART) treatment at enrolment (ART naïve, ≤3 months of ART, >3 months of ART) and time to starting ART (if ART naïve), enrolment CD4 count (median values and categories [<50, 51–100, 101–200, >200]), HIV viral load. These will be described in a baseline variable table (
Table 2).

**Table 2. T2:** Baseline characteristics template table.

Characteristic	Dexamethasone (N=XX)		Placebo (N=XX)	
	N	Summary statistic	N	Summary statistic
Age (years)	XX	XX (XX,XX)	XX	XX (XX,XX)
Sex - male	XX	XX (XX%)	XX	XX (XX%)
Country	XX	XX (XX%)	XX	XX (XX%)
Site - HTD - PNT - Cipto Mangunkusumo - Persahabatan	XX XX XX XX	XX (XX%) XX (XX%) XX (XX%) XX (XX%)	XX XX XX XX	XX (XX%) XX (XX%) XX (XX%) XX (XX%)
Diagnostic category - Definite TBM - Probable TBM - Possible TBM - Not TBM	XX XX XX XX	XX (XX%) XX (XX%) XX (XX%) XX (XX%)	XX XX XX XX	XX (XX%) XX (XX%) XX (XX%) XX (XX%)
Previous tuberculosis treatment	XX	XX (XX%)	XX	XX (XX%)
Chest X-ray findings - No tuberculosis - Miliary tuberculosis - Pulmonary tuberculosis	XX XX XX	XX (XX%) XX (XX%) XX (XX%)	XX XX XX	XX (XX%) XX (XX%) XX (XX%)
Modified MRC grade - Grade I - Grade II - Grade III	XX XX XX	XX (XX%) XX (XX%) XX (XX%)	XX XX XX	XX (XX%) XX (XX%) XX (XX%)
Glasgow coma score	XX	XX (XX,XX)	XX	XX (XX,XX)
Weight (kg)	XX	XX (XX,XX)	XX	XX (XX,XX)
Duration of symptoms (days)	XX	XX (XX,XX)	XX	XX (XX,XX)
Neurological signs - Cranial nerve palsy - Hemiplegia - Paraplegia/tetraplegia - Urinary retention	XX XX XX XX	XX (XX%) XX (XX%) XX (XX%) XX (XX%)	XX XX XX XX	XX (XX%) XX (XX%) XX (XX%) XX (XX%)
History of diabetes	XX	XX (XX%)	XX	XX (XX%)
HbA1c (%)	XX	XX (XX,XX)	XX	XX (XX,XX)
History of intravenous drug use	XX	XX (XX%)	XX	XX (XX%)
Hepatitis B sAg positivity,	XX	XX (XX%)	XX	XX (XX%)
Hepatitis C Ab positivity	XX	XX (XX%)	XX	XX (XX%)
Alanine aminotransferase (ALT) (IU/L)	XX	XX (XX,XX)	XX	XX (XX,XX)
Bilirubin (µmol/L)	XX	XX (XX,XX)	XX	XX (XX,XX)
Full blood count - Haemoglobin (g/dL) - White cell count (x10 ^3^/ µL) - Platelets (x10 ^3^/ µL)	XX XX XX	XX (XX,XX) XX (XX,XX) XX (XX,XX)	XX XX XX	XX (XX,XX) XX (XX,XX) XX (XX,XX)
Plasma sodium (mmol/L)				
*Leukotriene A4 hydrolase* - TT - CT - CC	XX XX XX	XX (XX%) XX (XX%) XX (XX%)	XX XX XX	XX (XX%) XX (XX%) XX (XX%)
CSF parameters - Opening pressure (cmH _2_0) - Total leucocytes (cells/mm ^3^) - Total neutrophils (cells/mm ^3^) - Total lymphocytes (cells/mm ^3^) - Protein (g/L) - Blood:CSF glucose	XX XX XX XX XX XX	XX (XX,XX) XX (XX,XX) XX (XX,XX) XX (XX,XX) XX (XX,XX) XX (XX,XX)	XX XX XX XX XX XX	XX (XX,XX) XX (XX,XX) XX (XX,XX) XX (XX,XX) XX (XX,XX) XX (XX,XX)
CSF microbiological tests - Positive ZN stain - Positive GeneXpert MTB/RIF - Positive GeneXpert MTB/RIF Ultra - Positive mycobacterial culture	XX XX XX XX	XX (XX%) XX (XX%) XX (XX%) XX (XX%)	XX XX XX XX	XX (XX%) XX (XX%) XX (XX%) XX (XX%)
Duration of anti-tuberculosis chemotherapy before enrolment (days)	XX	XX (XX,XX)	XX	XX (XX,XX)
Enrolment anti-tuberculosis chemotherapy regimen - Rifampicin - Isoniazid - Pyrazinamide - Ethambutol - Streptomycin	XX XX XX XX XX	XX (XX%) XX (XX%) XX (XX%) XX (XX%) XX (XX%)	XX XX XX XX XX	XX (XX%) XX (XX%) XX (XX%) XX (XX%) XX (XX%)
Anti-tuberculosis drug resistance * - Multi-drug resistant or rifampicin mono-resistant - Isoniazid resistant non-MDR - Pre-XDR - XDR - No or other resistance	XX XX XX XX XX	XX (XX%) XX (XX%) XX (XX%) XX (XX%) XX (XX%)	XX XX XX XX XX	XX (XX%) XX (XX%) XX (XX%) XX (XX%) XX (XX%)
HIV infection: new diagnosis or known positive status	XX	XX (XX%)	XX	XX (XX%)
ART status at enrolment - ART naïve - ≤3 months of ART - >3 months of ART - Unknown - Undetermined	XX XX XX XX XX	XX (XX%) XX (XX%) XX (XX%) XX (XX%) XX (XX%)	XX XX XX XX XX	XX (XX%) XX (XX%) XX (XX%) XX (XX%) XX (XX%)
Time to starting ART ^ # ^	XX	XX (XX,XX)	XX	XX (XX,XX)
Enrolment CD4 count (per mm ^3^)	XX	XX (XX,XX)	XX	XX (XX,XX)
Enrolment CD4 count (per mm ^3^) - <50 - 51–100 - 101–200 - >200	XX XX XX XX	XX (XX%) XX (XX%) XX (XX%) XX (XX%)	XX XX XX XX	XX (XX%) XX (XX%) XX (XX%) XX (XX%)
HIV viral load (copies/mL)	XX	XX (XX,XX)	XX	XX (XX,XX)

*Results given for sub-group with positive mycobacterial culture on baseline CSF. Pre-XDR and XDR are defined following World Health Organisation definitions
^
11
^.
^#^Results given for sub-group naïve to ART at enrolment. N = number of patients included in that statistic. Summary statistic = the median (1
^st^ and 3
^rd^ quartile) value for continuous data, and the number and frequency (%) of patients with the characteristic for categorical data. Definite TBM = positive acid fast bacilli (AFB) on CSF Ziehl Neelsen stain, or positive CSF TB GeneXpert test, OR positive CSF TB culture. Probable or possible TBM defined following uniform case defintion
^
10
^. Confirmed non-TBM = microbiologically confirmed other brain infection. Confirmed additional brain infection includes positive CSF India Ink stain, OR CSF cryptococcal antigen, OR positive blood cryptococcal antigen, OR positive CSF bacterial Gram stain, OR positive CSF bacterial culture, OR positive CSF viral or helminth PCR test. ART status of a patient will be unknown if i) they are on ART treatment and the start ART date is missing completely; or ii) their ART status is unknown. ART status of a patient will be undetermined if start ART date is present but distinction between ≤3 months of ART, and >3 months of ART, cannot be made due to limited date information. ART=antiretroviral therapy. HTD=Hospital for Tropical Diseases. MRC=Modified Research Council. PNT=Pham Ngoc Thach Hospital for Tuberculosis and Lung Disease. TBM=tuberculous meningitis. XDR=Extensively drug resistant. Xpert=Gene Xpert MTB/RIF. ZN=Ziehl Neelsen.

Analysis: Baseline characteristics will be summarised as median (lower and upper quartiles) for continuous data and frequency (percentage) for categorical data. The amount of missing data for each baseline characteristic will also be displayed. We will perform multiple imputation of a variable in case of >5% missing values, and it is assumed that data are missing at random. Otherwise, a complete case analysis will be performed.

### Use of the uniform case definition diagnostic score

The published TBM diagnostic score
^
10
^ will be used and subjects will be categorised as ‘definite’, ‘probable’, ‘possible’, or ‘not TBM’. Participants will only be categorised as ‘not TBM’ if they have a confirmed alternative diagnosis (alternative to TBM) or they recovered without TB drugs.

## Primary endpoint

The primary endpoint of this trial is death over the first 12 months after randomisation. The primary analysis is a Cox proportional hazards regression model with treatment as the only covariate. Since TBM MRC severity grade at enrolment (I, II, or III) is an important risk factor for mortality and was used as stratification variable in the randomisation, we will additionally perform a secondary analysis with MRC grade added as stratum variable. The proportional hazards assumption will be formally tested based on scaled Schoenfeld residuals and visually assessed by a plot of the scaled Schoenfeld residuals versus transformed time. Deaths, by study drug arm, and the results of the analyses will be shown as per
Table 3 and
Table 4. 

**Table 3. T3:** Hazard ratio for death (from any cause) over the first 12 months after randomisation.

	No. of deaths		Hazard ratio (95% CI); p value	Test for proportional hazards
	Dexamethasone	Placebo		
All patients Corrected for modified MRC grade	XX/XX	XX/XX	X.XX (X.XX, X.XX) X.XX (X.XX, X.XX)	X.XX X.XX

The primary endpoint will be overall survival, i.e., time from randomisation to death, over the first 12 months of follow-up. This table reports the results from the Cox proportional hazards regression model. The primary effect measure will be the resulting hazard ratio comparing dexamethasone vs. placebo with a corresponding two-sided 95% confidence interval. In "All patients", treatment will be the only covariate. We will additionally report the hazard ratio if the modified MRC grade is included as stratum variable. The test for proportional hazards will use the Kaplan-Meier as time transformation. MRC=Modified Research Council.

**Table 4. T4:** Hazard ratios for death (from any cause) by sub-group over the first 12 months after randomisation.

	No. of deaths		Hazard ratio (95% CI); p value	Test for proportional hazards	p-value for heterogeneity *
	Dexamethasone	Placebo			
Modified MRC grade: - Grade I - Grade II - Grade III	XX/XX XX/XX XX/XX	XX/XX XX/XX XX/XX	X.XX (X.XX, X.XX) X.XX (X.XX, X.XX) X.XX (X.XX, X.XX)	X.XX X.XX X.XX	X.XX
Diagnostic category - Definite TBM - Probable TBM - Possible TBM - Not TBM	XX/XX XX/XX XX/XX XX/XX	XX/XX XX/XX XX/XX XX/XX	X.XX (X.XX, X.XX) X.XX (X.XX, X.XX) X.XX (X.XX, X.XX) X.XX (X.XX, X.XX)	X.XX X.XX X.XX X.XX	X.XX
*Leukotriene A4 hydrolase* - TT - CT - CC	XX/XX XX/XX XX/XX	XX/XX XX/XX XX/XX	X.XX (X.XX, X.XX) X.XX (X.XX, X.XX) X.XX (X.XX, X.XX)	X.XX X.XX X.XX	X.XX
Anti-tuberculosis drug resistance ^ # ^ - Multi-drug resistant or rifampicin mono-resistant - Isoniazid resistant non-MDR - Pre-XDR - XDR - No or other resistance	XX XX XX XX XX	XX (XX%) XX (XX%) XX (XX%) XX (XX%) XX (XX%)	XX XX XX XX XX	X.XX X.XX X.XX X.XX X.XX	X.XX
ART status at enrolment - ART naïve - ≤3 months of ART - >3 months of ART	XX/XX XX/XX XX/XX	XX/XX XX/XX XX/XX	X.XX (X.XX, X.XX) X.XX (X.XX, X.XX) X.XX (X.XX, X.XX)	X.XX X.XX X.XX	X.XX
Enrolment CD4 count (per mm ^3^) - <50 - 51–100 - 101–200 - >200	XX/XX XX/XX XX/XX XX/XX	XX/XX XX/XX XX/XX XX/XX	X.XX (X.XX, X.XX) X.XX (X.XX, X.XX) X.XX (X.XX, X.XX) X.XX (X.XX, X.XX)	X.XX X.XX X.XX X.XX	X.XX

*Heterogeneity will be tested with a Cox regression model that includes an interaction between treatment effect and subgroup.
^#^Results will be given for sub-group with positive mycobacterial culture on baseline CSF. Pre-XDR and XDR are defined following World Health Organisation definitions
^
11
^. The primary endpoint will be overall survival, i.e., time from randomisation to death, over the first 12 months of follow-up. This table reports the results from the Cox proportional hazards regression model. The primary effect measure will be the resulting hazard ratio comparing dexamethasone vs. placebo with a corresponding two-sided 95% confidence interval. In these subgroup analyses, a separate Cox model will be fitted for each value of the subgroup. The "Test for heterogeneity" will be based on the likelihood ratio test that includes subgroup as covariate and compares the models with subgroup as main effect only and with subgroup as treatment effect modifier, with TBM MRC severity grade at enrolment (I, II, or III) as covariates. ART=antiretroviral therapy. MRC=Modified Research Council. TBM=tuberculous meningitis. XDR=extensively drug resistant.

Survivors known to be alive at 12 months will be censored at that time-point and subjects who withdrew or were lost to follow-up before 12 months will be censored at the date they were last known to be alive. Subjects who withdrew or were lost to follow-up before 12 months are estimated to be less than 5% of enrolled participants.

The homogeneity of the treatment effect on overall survival across subgroups will be assessed by formal tests of interaction between treatment and the following pre-defined grouping variables: TBM MRC severity grade at enrolment (I, II, or III), diagnostic category (definite, probable, possible),
*LTA4H* genotype (CC/CT/TT), drug resistance pattern (MDR TB or rifampicin mono-resistant TB, isoniazid resistant non-MDR, no or other resistance), ART status at enrolment (ART naïve, ≤3 months of ART, >3 months of ART), and CD4 cell count at enrolment (<50, 51–100, 101–200, >200). We will estimate and report the treatment effect by fitting a separate Cox model per subgroup. We will additionally fit a Cox model that includes CD4 count at enrollment as a continuous variable via a restricted cubic spline with four knots and an interaction term with treatment arm.

Kaplan-Meier plots and explicit survival estimates at 3, 6, and 12 months of follow-up will be calculated for the full sample and in the subgroups defined above. We will compare the treatment arms via the absolute risk of death at 12 months (using a Wald-type test based on Kaplan-Meier estimates at 12 months and associated standard errors using Greenwood’s formula) and the restricted mean survival until 12 months (using the survRM2
^
12
^ package in R).

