### 1. Neurological disability at 12 months from randomisation

Neurological disability will be assessed by the modified Rankin score at months 1, 2, 3, 6, 9, and 12 from randomisation (
Table 5). The main secondary endpoint is the 12-month assessment and subjects who died before 12 months will be treated as having a score of 6 (‘dead’). Rankin score assessments will be included from clinical assessments performed monthly (+/- 7 days), with the exception of the 12-month clinical assessment for which an acceptable range of -10 days/+1 month will be applied. All clinical assessment timings are based on days from randomisation (i.e., ‘day 0’ is labeled as the first day study drug is received, with study drug received immediately after randomisation).

**Table 5. T5:** The Modified Rankin Scale.

Score	Description
0	No symptoms
1	Minor symptoms not interfering with lifestyle
2	Symptoms that lead to some restriction in lifestyle, but do not interfere with the patients ability to look after themselves
3	Symptoms that restrict lifestyle and prevent totally independent living
4	Symptoms that clearly prevent independent living, although the patient does not need constant care and attention.
5	Totally dependent, requiring constant help day and night.
6	Death

Neurological disability (as assessed by the ordinal modified Rankin scale) at 12 months will be compared between the two arms with a proportional odds logistic regression model with the treatment assignment as the main covariate and adjustment for TBM MRC severity grade. The result will be summarised as a cumulative odds ratio with corresponding 95% confidence interval and p‐value. Individuals who withdrew or were lost to follow-up before 12 months are excluded.

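### The primary Cox model leaves out the randomisation strata, so the mortality test is valid but conservative; the MRC-stratified model already planned for Table 3 should be primary

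*SAP article*

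**What the plan says.** All references are to the SAP article.

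- *Structure and status of trial*: "Randomisation was stratified by TBM MRC severity score and by hospital". The same section gives the size: "the predefined sample size of 520 adults with TBM and HIV co-infection had been enrolled from four hospitals".
- *Primary endpoint*: "The primary analysis is a Cox proportional hazards regression model with treatment as the only covariate". The next sentence begins "Since TBM MRC severity grade at enrolment (I, II, or III) is an important risk factor for mortality", adds that grade was a randomisation stratum, and concludes "we will additionally perform a secondary analysis with MRC grade added as stratum variable". Table 3 prints both hazard ratios.
- *Secondary endpoints, 1. Neurological disability*: the Rankin model is fitted "with the treatment assignment as the main covariate and adjustment for TBM MRC severity grade".
- *Table 4 footnote*: the heterogeneity test compares models "with TBM MRC severity grade at enrolment (I, II, or III) as covariates". The subgroup hazard ratios in the same rows come from a separate Cox model per subgroup, with no grade adjustment stated.
- Hospital is listed as a baseline characteristic (Table 2) but appears in no outcome model.

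**The concern.** The plan states the reason for stratifying the mortality analysis by grade and then does not apply it to the confirmatory test. Stratified randomisation balances the arms within grade and hospital, which reduces the chance variation of the treatment comparison. A model without those factors computes its standard error as if that balance had not been imposed. When the strata are prognostic, the standard error is therefore too large for the design and the test rejects too rarely. Separately, leaving a prognostic factor out of a Cox model gives a marginal hazard ratio nearer to 1 than the within-stratum one whenever there is an effect.

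At stake is the chance of detecting a real mortality effect. If the two rows of Table 3 fall on either side of 0.05, the plan makes the more conservative row decisive. The plan is also uneven: the Rankin model and the heterogeneity tests use grade and the primary model does not. Within a Table 4 row, the estimates and the p-value for heterogeneity come from differently adjusted models.

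**Working it through.** **Inputs from the SAP article.** N = 520; four hospitals; strata MRC grade and hospital; two-sided 95% interval; loss to follow-up below 5%; background mortality "with mortality approaching 50% in people living with HIV". The document gives no target hazard ratio, power, event count, grade mix or mortality by grade, so the 520 cannot be reproduced.

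**Context.** Approximate power for 1:1 allocation with d deaths is Φ(|ln HR|·√d/2 − 1.96). At an assumed HR of 0.70, |ln HR| = 0.3567.
- 40% mortality: d = 520 × 0.40 = 208, so 0.3567 × 14.42/2 = 2.57 and power = Φ(0.61) = 73%.
- 50% mortality: d = 520 × 0.50 = 260, so 0.3567 × 16.12/2 = 2.88 and power = Φ(0.92) = 82%.

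In this range a few points of power matter.

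**Simulation.** 3,000 trials per scenario, permuted blocks of 4 within grade × hospital, front-loaded Weibull deaths, censoring at 12 months, 3% loss. Assumed, not from the document: placebo mortality by grade I/II/III of 40/50/60% (weak), 30/50/70% (moderate) or 25/50/80% (strong); grade mix 40/40/20, or 35/40/25 for the strong case; no hospital effect, or hospital log-hazard differences of ±0.3.

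Results at a true within-grade HR of 0.70 (SE = mean model-based standard error of the log HR; SD = its actual spread over trials):

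| Gradient | Model | HR | SE | SD | SE/SD | Power |
|---|---|---|---|---|---|---|
| Weak | treatment only | 0.703 | 0.1368 | 0.1352 | 1.01 | 73.4% |
| Weak | MRC-stratified | 0.700 | 0.1369 | 0.1364 | 1.00 | 74.4% |
| Moderate | treatment only | 0.711 | 0.1396 | 0.1335 | 1.05 | 69.7% |
| Moderate | MRC-stratified | 0.698 | 0.1398 | 0.1401 | 1.00 | 74.0% |
| Strong | treatment only | 0.726 | 0.1345 | 0.1227 | 1.10 | 67.4% |
| Strong | MRC-stratified | 0.698 | 0.1349 | 0.1344 | 1.00 | 76.3% |
| Strong + hospital | treatment only | 0.728 | 0.1377 | 0.1259 | 1.09 | 64.7% |
| Strong + hospital | MRC-stratified | 0.703 | 0.1380 | 0.1371 | 1.01 | 72.1% |
| Strong + hospital | MRC × hospital | 0.698 | 0.1392 | 0.1398 | 1.00 | 72.3% |

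Power differences: 74.4 − 73.4 = 1.0; 74.0 − 69.7 = 4.3; 76.3 − 67.4 = 8.9 points. Adding hospital to grade: 72.3 − 72.1 = 0.2 points.

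**Under no effect**, the treatment-only test rejects 3.9% (weak), 4.2% (moderate), 3.1% (strong) and 2.7% (strong + hospital) instead of 5%. MRC stratification gives 4.3%, 5.2%, 4.7% and 4.2%; MRC × hospital gives 4.3%, 5.0%, 5.2% and 5.1%. The Monte Carlo standard error is √(0.05 × 0.95/3000) = 0.4 points, so the weak case barely separates the models.

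**Where the gain comes from.** Power is close to Φ((|ln HR| − 1.96·SE)/SD). Moderate case:
- treatment only: (0.3414 − 1.96 × 0.1396)/0.1335 = 0.51, Φ = 69%;
- MRC-stratified: (0.3600 − 1.96 × 0.1398)/0.1401 = 0.61, Φ = 73%.

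The standard errors are almost equal, and so are the interval widths on the log scale (0.547 and 0.548). What changes is the estimate: 0.3414 against 0.3600.

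**Sensitivity.** A second set of 3,000-trial simulations used mortality of 35/50/60%, 30/50/70% and 25/50/80%, modest hospital effects and a different Weibull shape. At HR 0.70 the treatment-only HR averaged 0.706, 0.717 and 0.727. Power was 70%, 68% and 64% against 72%, 72% and 73% stratified by grade: losses of 2, 4 and 9 points. Null rejection was 4.6%, 3.8% and 2.5%.

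**The case against.** The strongest reply is that the plan already deals with grade. The same section gives the reason, pre-specifies the MRC-stratified model, and prints both results in Table 3. For grade, the dispute is only which line is called primary, and the authors chose openly. That is fair, and it makes the remedy cheap. It does not answer why the confirmatory line is the one that ignores the design.

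Four stronger readings are tempting, and the documents do not support them.

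- *A reader might infer that stratifying would narrow the reported interval.* It would not; on the log scale the widths are practically the same. The treatment-only interval is too wide only relative to that estimator's own sampling error.
- *A reader might infer that the treatment-only hazard ratio is biased or its test invalid.* It is a legitimate marginal estimate, the plan nowhere claims a conditional one, and the error is in the conservative direction. Nor is it shown to be the least efficient estimate: in the moderate case, log HR over true SD is 0.3414/0.1335 = 2.56 against 0.3600/0.1401 = 2.57. The reported standard error simply does not credit the precision gained by the design.
- *A reader might infer that omitting hospital costs much.* In the scenario with a hospital effect, adding hospital to grade changed power by under 1 point. The case for hospital is consistency with the randomisation.
- *A reader might infer that every model should be stratified by grade and hospital.* Three grades by four hospitals make 12 strata. In small Table 4 rows or rare outcomes such as malignancy or shunt surgery, many strata could hold too few events to inform the comparison. This was not tested and could discard information.

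It also stands that the 9-point loss needs a steep gradient that the SAP does not document.

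**Conclusion.** The point holds as a recommendation on efficiency and consistency with the design, not as an error that threatens validity. The treatment-only primary test is conservative: at HR 0.70 its standard error is about 1% too large for a weak gradient, 5% for a moderate one and 9 to 10% for a strong one. A within-grade HR of 0.70 is reported as about 0.70 to 0.73. The power lost is about 1 to 2, 4 and 9 points respectively, nearly all through MRC grade.

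The direction follows from stratified randomisation on a prognostic factor, which the plan itself acknowledges. The size rests on assumed mortality by grade, grade mix and true effect, none of which the document gives. If grade is only weakly prognostic in this population, the loss is negligible.

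The Table 4 mismatch is minor. It is disclosed in the footnote, and the MRC rows are within-grade by construction.

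**What to change.** Before unblinding:

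1. Make the MRC-stratified Cox model already planned for Table 3 the primary analysis. Also stratify it by hospital, or by country if grade-by-hospital cells are sparse, to match the randomisation.
2. Keep the treatment-only Cox model as the supportive line in Table 3.
3. In Table 4, stratify the subgroup hazard ratios by MRC grade (except in the MRC rows) where event counts allow, so that they match the MRC-adjusted heterogeneity test.
4. Do not require grade-by-hospital stratification for small subgroups or rare secondary outcomes.

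The cost is a change of wording; grade and hospital are already recorded for every patient because they were used to randomise. The downside is that the primary hazard ratio becomes conditional on the strata and should be described so. The unadjusted hazard ratio is still reported beside it.
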